## Abstract

**Background:**

Non-adherence to Tuberculosis (TB) medication is a serious threat to TB prevention and control programs, especially in resource-limited settings. The growth of the popularity of mobile phones provides opportunities to address non-adherence, by facilitating direct communication more frequently between healthcare providers and patients through SMS texts and voice phone calls. However, the existing evidence is inconsistent about the effect of SMS interventions on TB treatment adherence. Such interventions are also seldom developed based on appropriate theoretical foundations. Therefore, there is a reason to approach this problem more rigorously, by developing the intervention systematically with evidence-based theory and conducting the trial with strong measurement methods.

**Methods:**

This study is a single-blind parallel-group design individual randomized control trial. A total of 186 participants (93 per group) will be individually randomized into one of the two groups with a 1:1 allocation ratio by a computer-generated algorithm. Group one (intervention) participants will receive daily SMS texts and weekly phone calls concerning their daily medication intake and medication refill clinic visit reminder and group two (control) participants will receive the same routine standard treatment care as the intervention group, but no SMS text and phone calls. All participants will be followed for two months of home-based self-administered medication during the continuation phases of the standard treatment period. Urine test for the presence of isoniazid (INH) drug metabolites in urine will be undertaken at the random point at the fourth and eighth weeks of intervention to measure medication adherence. Medication adherence will also be assessed by self-report measurements using the AIDS Clinical Trial Group adherence (ACTG) and Visual Analogue Scales (VAS) questionnaires, and clinic appointment attendance registration. Multivariable regression model analysis will be employed to assess the effect of the Ma-MAS intervention at a significance level of P-value < 0.05 with a 95% confidence interval.

**Discussion:**

For this trial, a mobile-assisted medication adherence intervention will first be developed systematically based on the Medical Research Council framework using appropriate behavioural theory and evidence. The trial will then evaluate the effect of SMS texts and phone calls on TB medication adherence. Evidence generated from this trial will be highly valuable for policymakers, program managers, and healthcare providers working in Ethiopia and beyond.

**Trial registration:**

The trial is registered in the Pan-Africa Clinical Trials Registry with trial number PACTR202002831201865.

## Background

Non-adherence to Tuberculosis (TB) treatment is a risk factor for further transmission, treatment failure, relapse, acquired multi-drug resistance, or extensively drug-resistant TB and death [1–3]. In Ethiopia, non-adherence to TB treatment, specifically a medication regimen involving a combination of antibiotics, is a serious threat to TB prevention and control programs. A recent systematic review and meta-analysis conducted in Ethiopia found that the pooled prevalence of non-adherence to TB medication was 21.3% [4].

Non-adherence to TB treatment is influenced by many interconnected factors. These include patient-centred-related factors, economic-related factors, social-related factors, health system-related factors, therapy-related factors, geographical access-related factors and lifestyle-related factors [5, 6]. The major factors affecting TB treatment adherence in Ethiopia are patient-centred-related factors such as knowledge about TB, its treatment duration and consequence of non-adherence [7–9], educational status [7, 10], psychological state of the patients like forgetfulness [10–13] and psychological distress [7, 14] and social-related factors such as social support, stigma and discrimination, perceived risk, perceived wellness/cure, and perceived barriers over the benefits [7, 14].

The World Health Organization (WHO) recommended Direct Observation of Treatment (DOT) by a trained supervisor; a health worker or a treatment supporter watches the patient take their antibiotics every day to ensure adherence [15]. However, evidence shows that DOT does not necessarily provide a reliable solution to poor TB treatment adherence [16, 17]. In Ethiopia, implementing DOT is also very challenging for patients as it requires patients’ daily visits to the health facility, which has undesired implications in their work, social life and high transportation cost [18, 19]. The current WHO recommendations are to consider DOT implementation with different administration options including conventional DOT, video-observed treatment (VOT), and non-daily DOT [20]. The non-daily DOT has been implemented in Ethiopia, in which during the first two months of the intensive phase of treatment patients take their daily medications with the supervision of the healthcare provider, and from two to six months in the continuation phase of treatment patients take all their medications at home and visit a clinic weekly to refill their medications [11, 19]. However, the non-daily DOT schedule has been interrupted by the COVID-19 pandemic [21].

Digital health interventions through mobile health can create new opportunities for healthcare improvements, especially in situations with limited infrastructure, expertise, and human resources in the healthcare system [22–25]. Digital health interventions that enhance TB medication adherence are seen as a promising option to bring health benefits to the community [26]. The growth in popularity of mobile phones provides opportunities to address adherence challenges related to DOT, as mobile health can facilitate direct communication between healthcare providers and TB patients through SMS and voice calls along with DOT or non-daily DOT [27, 28]. Along with SMS text reminders, phone calls are also suggested to improve a patient’s clinic attendance and treatment outcomes, and can also be used to make the SMS text intervention interactive [29, 30]. In Ethiopia, access to mobile phones is expanding widely: according to the Ethiopia Demography Health Survey (EDHS) 2016, 88% of urban households and 47% of rural households have mobile phone access [31]. This is substantial growth over 5 years when compared to the EDHS 2011, which indicated 65% of urban households and 13% of rural households had mobile phone access [32].

There is some evidence that interventions that rely on communications, like educating and counselling the patient, or medication monitoring and reminders, can improve treatment adherence and success [28, 33–35]. In Ethiopia, for example, a randomized trial in 2016 found that psychological counselling and educational intervention can significantly improve a patient’s treatment adherence [36]. Another trial in Ethiopia in 2019 has investigated the effect of a daily SMS text and weekly medication refill reminders on patient’s medication adherence [37]. However, the combination of SMS text and phone calls (as in the intervention proposed here) based on the application of formal behavioural theories and behavioural techniques has not been previously designed and tested. This trial will also apply a combination of direct and indirect methods of adherence measurements for outcomes assessment. The mobile-assisted medication adherence support intervention will be developed systematically based on the Medical Research Council model, incorporating appropriate theory and evidence. The intervention design will be informed through qualitative in-depth interviews with different stakeholder groups such as patients, healthcare providers and healthcare managers, and the SMS content will be validated with experts in behavioural science, healthcare system, pulmonary disease and digital health, using a Delphi technique and will be revalidate by health professionals working at ground level.

## Methods

### Hypothesis

We plan to test whether our Mobile-assisted Medication Adherence Support (Ma-MAS) intervention using mobile SMS text reminders and phone calls will improve Tuberculosis medication adherence in addition to routine standard non-daily DOT care.

### Trial design

A parallel-group individual randomized controlled trial (RCT) with two groups will be employed to investigate the effect of Ma-MAS intervention on TB medication adherence. Participants will be individually randomized into one of the two groups (one intervention and one control group) in a 1:1 allocation ratio (Fig 1).

**Fig 1 pone.0261758.g001:**
[figure not shown]
Timeline for Ma-MAS intervention trial (SPIRIT figure).

### Study setting

The study will be conducted at the primary public health facilities of Addis Ababa, Ethiopia. Addis Ababa is the capital city of Ethiopia, and the city has 11 administrative sub-city regions. Based on population projection the estimated total population of Addis Ababa in 2017 was 3,433,999 with 1,624,999 Males and 1,809,000 Females [38]. In Ethiopia, a DOT program has been implemented in two phases, “intensive” and “continuation”. In the intensive phase (daily DOT), a patient takes their medication in front of the healthcare worker every day at a health facility. In the continuation phase (non-daily DOT), a patient is given the responsibility to take the medication at home and come to a health facility weekly for health checking and medication refilling [39].

### Participants

Adult Tuberculosis patients who are receiving anti-TB treatment at primary public health facilities of Addis Ababa, Ethiopia will be prospective participants for the trial.

### Eligibility

#### Inclusion criteria

To be included in the trial:

participants must be enrolled in a primary public health facility for anti-TB treatment and have attained their first two months of the intensive phase of treatmentparticipants must be aged 18 years and aboveparticipants must be able to read and understand SMS text that is written in the national official language (Amharic) of Ethiopiaparticipants must have their own mobile phone, orparticipants who do not have a mobile phone can be included if they have a shared mobile phone in the household with a collaborative agreement; (i.e. a voluntary agreement between the patient and family member living in the same household).

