#### Exclusion criteria

Participants will be excluded from the trial under the following conditions:

participants whose anti-tuberculosis treatment has been underway for more than six months.participants who are enrolled or have agreed to enroll in any other interventional study at the same time as this study is conducted.

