### Control group

The control group (Arm-2) participants will receive the same routine standard treatment care as the intervention group, but no SMS text and phone calls intervention. Patients in the control group will be followed for the same two-month period as the intervention group during the continuation phase of their treatment.

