### Randomization and allocation

Participants will be centrally randomized into one of the two groups using simple randomization in computer-generated algorithm, with an equal allocation ratio (1:1), by members of the research support team, who will not be involved in measuring the outcome (Fig 4).

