### Follow up

Both the intervention and control groups’ patients will be followed for an equal period of 2 months. Intervention group participants will receive a total of 60 daily SMS text reminders and 8 phone calls for medication intake and refill visits reminders.

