### Implementation

All patients assigned to any group will get the same standard treatment based on the Ethiopia National Tuberculosis Treatment guideline which is rifampicin, isoniazid, pyrazinamide and ethambutol for two months followed by rifampicin and isoniazid for four months [50]. Patients screening, enrolment, consenting and randomization will be undertaken by the research support team, who have health professional backgrounds. An open SMS automation software platform will be used to store, monitor, and send SMS texts. Global system for mobile (GSM) sim card and short code SMS credit will be used to send the SMS texts. SMS text traffic will be managed and monitored in one centralised computer database server by trained IT personnel. The maximum size of an SMS text will not be more than 160 characteristics. A weekly phone calls will be made to the intervention group participants from the health facility by delegated members of the research team. A checklist of questions will be recorded at each time the weekly phone calls are made to the participants (S2 Checklist). Bothe the SMS text and Phone calls intervention will be made using the national official language which is Amharic. For patients who do not answer phone calls, three repetitive attempts will be made at five-minute intervals. All SMS texts and phone calls will be delivered at a similar time in the morning before the actual medication time. The message delivery reports will be continuously monitored to ensure the participants have received the SMS texts as planned. Participants will also be asked whether they are receiving the SMS text every week through phone calls and when they come for their medication refill visit. Participants will be briefed on the duration, frequency, and timing of SMS text and phone calls intervention and advised to turn on their mobile in the morning. Participants will be informed about the intervention and instructed not to tell and/or share the SMS texts or phone calls with other people. If participants lose or change their phone numbers, the new phone number will be replaced immediately after they have informed a support team member. The trial will be audited with participant enrolment, consent, allocation, and during the intervention period.

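### Shared household phones are admitted, but nothing keeps two members of one household out of opposite arms, so a control could see the other member's texts; the effect is probably small and the fix is cheap

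*Protocol article*

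**What the plan says.** All references are to the Protocol article.

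- **Inclusion criteria.** A patient without a phone "can be included if they have a shared mobile phone in the household with a collaborative agreement". The agreement is described as "a voluntary agreement between the patient and family member living in the same household".
- **Exclusion criteria.** There are two. One is treatment that has run for more than six months. The other is "participants who are enrolled or have agreed to enroll in any other interventional study at the same time as this study is conducted". Neither concerns a second patient in the household or on the same number.
- **Trial design; Randomization and allocation.** The individual is the unit: "Participants will be centrally randomized into one of the two groups using simple randomization in computer-generated algorithm", in a 1:1 ratio. No household unit or restriction is described.
- **Control group.** Controls get the same routine care, "but no SMS text and phone calls intervention".
- **Follow up.** "Intervention group participants will receive a total of 60 daily SMS text reminders and 8 phone calls".
- **Implementation.** Participants are "instructed not to tell and/or share the SMS texts or phone calls with other people". No exception is made for the family member with whom a phone is shared.

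**The concern.** The trial compares people who get reminders with people who do not. Among the measures that the article describes, the instruction not to share is the one that bears on whether controls see the reminders. Blinding of the outcome assessor protects measurement, not exposure.

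On a shared phone that protection is weaker, because the texts arrive on a device that someone else in the household also uses. If that other person is a TB patient enrolled as a control, the control condition can no longer be assured. Individual simple randomisation does not prevent this and the eligibility criteria do not rule it out. An exposed control who takes medication more reliably as a result narrows the difference between arms, so the bias runs toward no effect.

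There is also a wording problem. A participant told to keep the messages from other people, while using a family member's phone by agreement, has no guidance on whether that family member counts as one of those people.

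**Working it through.** **1. Can a household pair be split?** Both members can meet the inclusion criteria, and neither exclusion applies to them as a pair. Under independent 1:1 allocation:

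P(opposite arms) = 2 × 0.5 × 0.5 = 0.5.

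So *k* co-enrolled pairs give on average *k*/2 controls who live with an intervention participant. The article does not give *k*. One exposed control corresponds to about two pairs, and two exposed controls to about four.

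**2. The plan's own figures.** Sample size gives 25.6% v 10.6% non-adherence (a 15-point difference), 81 per arm before attrition and 93 per arm after 15% attrition. With the pooled-variance formula and 80% power, a one-sided 0.05 test needs 81 per arm, while the stated one-sided 0.025 needs 103. The stated 81 is therefore not reproduced at its stated level. That is a separate matter. It is noted here only because it sets the baseline power below.

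**3. Evaluable controls.** 93 × (1 − 0.15) = 79.05, taken as 79.

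**4. Contrast under exposure.** Let *c* be the share of controls exposed, and suppose each gains the full 15-point benefit. This is an upper bound. Control non-adherence is then 0.256 − 0.15*c*, and the contrast is 15 × (1 − *c*) points.

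- 1 exposed: *c* = 1/79 = 0.0127, contrast 14.8 points.
- 2 exposed: *c* = 2/79 = 0.0253, contrast 14.6 points.

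**5. Power with *n* = 79 per arm.**

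Power = Φ{[d − z√(2p̄(1−p̄)/n)] / √([p₁(1−p₁) + p₂(1−p₂)]/n)}

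With no exposure and a two-sided 5% test, d = 0.15 and p̄ = 0.181. The null standard error is √(2 × 0.181 × 0.819/79) = 0.0613 and the alternative one is √((0.1905 + 0.0948)/79) = 0.0601. Power = Φ[(0.15 − 1.96 × 0.0613)/0.0601] = 69.1%.

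| Controls fully exposed | Control rate | Contrast (points) | Power, two-sided 5% | Power, one-sided 5% |
|---|---|---|---|---|
| 0 | 25.6% | 15.0 | 69.1% | 79.4% |
| 1 | 25.4% | 14.8 | 68.1% | 78.6% |
| 2 | 25.2% | 14.6 | 67.2% | 77.8% |

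On either significance level the loss is about 1 to 2 points.

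**6. Would a large exposure be plausible?** Eight exposed controls (*c* about 10%, contrast 13.5 points, two-sided power about 61%) would need about 16 evaluable same-household pairs. That is 32 of 158 evaluable participants, or 20%. Over the 36 facilities planned under Sample size, it is a pair at about 16/36 = 44% of them. Nothing in the article suggests this.

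**7. The two sections side by side.** Inclusion criteria makes one named family member a party to the phone arrangement. Implementation forbids sharing with other people, without qualification. Read literally, a participant on a shared phone may be unable to comply. Read with the agreement in mind, other people means those outside it. The text does not say which is meant.

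**The case against.** The best case against the point has four parts.

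*The phone holder is usually not in the trial.* A family member who sees a text but is not a participant contaminates nothing. Exposing a control needs a chain of events: two adult TB patients in one household, both eligible, enrolled over overlapping two-month periods, sharing a phone or seeing each other's messages, and randomised apart. This stands, and it is why the expected size is small. Admitting shared phones does not by itself deliver the intervention to any control.

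*Exposure is not treatment.* A reader might infer that a control on a shared phone is in effect treated. The article does not support that. The weekly calls are made to intervention participants, and reading texts meant for someone else is partial exposure. The calculation above is therefore a ceiling.

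*The two sections can be read together.* A reader might infer a flat contradiction that defeats the safeguard. That is too strong, because the agreement already makes the family member a known party. What remains is an unqualified instruction that needs a clarifying phrase.

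*A rule of one participant per household is operational detail.* The full protocol may contain one, and its absence from an article is weak evidence that none exists. This has some force. But the article does set out its eligibility criteria, and it expressly admits the shared phones that open this route, so a matching exclusion belongs beside them.

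**Conclusion.** The point holds as a minor one. As stated, the eligibility and randomisation rules let two members of a household be enrolled and, with probability 0.5, put in opposite arms. A control could then be exposed to the other member's texts, with bias toward no effect. If 1 to 2 controls were exposed, the contrast would fall from 15 to no lower than about 14.8 to 14.6 points, and power would fall by about 1 to 2 points. This rests on three assumptions: 79 evaluable controls, a full benefit for each exposed control, and a number of exposed controls that the article does not give and that is probably low.

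Three stronger conclusions should not be drawn. A fall in power from 69% to 61% needs an implausible number of pairs. The 69% starting point comes from the separate sample-size discrepancy, not from contamination. And although paired participants are not strictly independent, a handful of pairs among 186 would have a negligible effect on the variance.

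The mismatch between the shared-phone agreement and the instruction not to share depends on no rate. It is a matter of wording to be reconciled.

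**What to change.** 1. Under Exclusion criteria, add that a patient is not enrolled when a member of the same household, or a user of the same phone number, is already in the trial.
2. Check this at registration by matching the phone number against the central SMS database that Implementation describes. Controls' numbers must be recorded for the match to work. Also ask at enrolment whether another household member is on TB treatment or in the trial, which catches pairs on different phones.
3. Under Implementation, word the instruction so that it covers the participant and, where a phone is shared, the family member who is party to the agreement, and asks both not to pass the content on to others.

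The cost is one eligibility line, a number check, one question and one sentence. The downside is that a few second household members are not enrolled.

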#### Exclusion criteria

Participants will be excluded from the trial under the following conditions:

participants whose anti-tuberculosis treatment has been underway for more than six months.participants who are enrolled or have agreed to enroll in any other interventional study at the same time as this study is conducted.

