### Intervention group

The intervention will be given in arm-1 (intervention) group participants will receive a daily SMS text and weekly phone calls for medication intake and medication refill visit reminders. All participants will receive the intervention at a similar time for two months during the continuation phase of anti-TB treatment (Fig 2).

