### Outcome

The outcome of the trial is the medication adherence of the patient, measured by both direct and indirect methods of measurement. The primary outcome will be measured using an IsoScreen test (GFC Diagnostics Ltd, Bicester, England) for the presence of isoniazid (INH) drug metabolites in urine in accordance with the vendor-supplied user manual. The IsoScreen test result is negative when there is no colour change (i.e. the strip remains yellow) after 5 minutes, and the test result is positive when the colour changes to dark purple, or blue/ green in that time, depending on the concentration of the medication (i.e. if the medication was taken in the last 24 hours or 48 hours respectively) [44, 45]. The IsoScreen test will be done at the fourth and eighth weeks of the intervention. The proportion of adherence measured by the IsoScreen test at the eighth week of the intervention (primary end point) will be used as the primary interest of analysis. The proportion of adherence measured by the IsoScreen test at the fourth week of the intervention will be used as the secondary interest of analysis.

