### Recruitment

Patients enrolled in the intensive phase of anti-TB treatment will be recruited by the research support team of healthcare professionals from each health facility, based on the eligibility and exclusion criteria. The recruitment will be continued until the required sample size is obtained. All the recruitment process details will be recorded on paper forms and kept securely by the facilities until the project is completed.

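### The six-month limit on prior treatment equals the whole isoniazid course, so eligibility does not ensure that patients are still prescribed isoniazid at the week-8 urine test

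*Protocol article*

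**What the plan says.** All references are to the Protocol article.

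- **Exclusion criteria.** The only ceiling on time on treatment removes "participants whose anti-tuberculosis treatment has been underway for more than six months".
- **Inclusion criteria.** The floor is that the first two months (the intensive phase) have been attained. No criterion asks how much treatment remains.
- **Implementation.** The regimen is "rifampicin, isoniazid, pyrazinamide and ethambutol for two months followed by rifampicin and isoniazid for four months", so isoniazid is scheduled for six months in all. The Background agrees: "from two to six months in the continuation phase of treatment patients take all their medications at home".
- **Outcome.** "The IsoScreen test will be done at the fourth and eighth weeks of the intervention", and the week-8 result is the primary endpoint. The test reflects recent intake: the colour depends on "if the medication was taken in the last 24 hours or 48 hours respectively". No provision is made for a patient whose course has ended.
- **Intervention group.** "All participants will receive the intervention at a similar time for two months during the continuation phase of anti-TB treatment". The Control group section and the Abstract likewise place two months of follow-up inside the continuation phase.
- **Recruitment.** "Patients enrolled in the intensive phase of anti-TB treatment will be recruited by the research support team", and this is done according to the eligibility and exclusion criteria.

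**The concern.** A week-8 urine test measures adherence only if isoniazid is still prescribed at week 8. A six-month ceiling on a six-month course does not secure that. A patient who enters at month 5 meets both listed criteria, may take every remaining dose, finishes on schedule, and then has nothing to detect when the primary sample is taken. Under the stated scoring, that patient counts as non-adherent.

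The same patient has no weekly refills left to attend, so the attendance outcome loses its meaning, as do the medication and refill reminders. The Statistical analysis section keeps all randomised participants by intention to treat, so such patients could not be set aside afterwards without departing from the plan. Each one adds the same event to whichever arm they join, which pulls the two observed proportions together.

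**Working it through.** **Timing.** Inputs: isoniazid ends at month 2 + 4 = 6 (Implementation); the primary test is at week 8, or 56 days (Outcome). I take a month as 30.44 days and entry as the start of the intervention.

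- 56 / 30.44 = 1.84 months.
- Latest entry for which week 8 falls within the course: 6 − 1.84 = month 4.16. Allowing a 48-hour detection window: 6 − 54/30.44 = month 4.23.
- Entry at month 2 puts the test at month 3.84; month 4 at 5.84; month 5 at 6.84; month 6 at 7.84.

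The criteria therefore leave open a window from about month 4.16 to month 6 in which the primary test comes after the last scheduled dose.

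**Baseline power.** Inputs from Sample size: non-adherence 25.6% versus 10.6%, 81 per arm, raised to 93 for 15% attrition. The stated 81 is reproduced only with a one-sided 0.05 test; the stated one-sided 0.025, equivalent to two-sided 0.05, needs 103 per arm. That is a separate matter, but it sets the baseline here. Evaluable per arm: 93 × 0.85 = 79.

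Power = Φ{[d√n − 1.96√(2p̄(1 − p̄))] / √(p₀(1 − p₀) + p₁(1 − p₁))}, where d = p₀ − p₁ and p̄ is the mean of the two proportions.

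At n = 79: (1.333 − 1.067) / 0.534 = 0.498, so power is 69%.

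**Effect of late entrants.** Let f be the share in each arm whose course has ended by week 8 and who therefore test negative. The article gives no value for f, so it is varied.

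- Observed non-adherence = f + (1 − f)p.
- Observed difference = (1 − f) × 15 points.

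| f | Control | Intervention | Difference (points) | Power, 79 per arm, two-sided 0.05 |
|---|---|---|---|---|
| 0 | 25.6% | 10.6% | 15.0 | 69% |
| 5% | 29.3% | 15.1% | 14.25 | 58% |
| 10% | 33.0% | 19.5% | 13.5 | 49% |
| 25% | 44.2% | 33.0% | 11.25 | 30% |
| 46% | 59.8% | 51.7% | 8.1 | 17% |

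Example, f = 25%: (1.000 − 1.349) / 0.684 = −0.511, so power is 30%.

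The last row is what uniform entry over months 2 to 6 would give: 1.84 / 4 = 46% (44% with the 48-hour allowance). It illustrates the outer end of the range and is not a forecast.

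**The case against.** The strongest reply is that the article, read as a whole, does not intend late entry. Three sections place two months of intervention or follow-up inside the continuation phase for all participants, and a patient entering at month 5 cannot satisfy them. The Recruitment section draws on patients in the intensive phase. Identifying them there and entering them once two months are complete is coherent, and puts week 8 near month 3.84. The timeline and flow figures are not shown and might state the entry month.

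Much of this stands. A reader might infer from the exclusion limit alone that completers will be enrolled and the primary endpoint will be misclassified. The article does not support that: it could happen, and if recruitment runs as the Recruitment section suggests, f is zero. Nor does it support treating half the sample as late entrants, because no section gives an entry distribution. A bias in favour of either arm cannot be inferred, since randomisation makes f similar across arms in expectation.

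What the reply does not do is remove the inconsistency. The Recruitment section works through the eligibility and exclusion criteria, so it does not clearly override the ceiling. The two-month statements describe what is meant to happen, but no criterion enforces them. If everyone entered at about month 2, a six-month exclusion would have nothing to exclude. Its presence tells screeners at 36 facilities that months 4 to 6 are acceptable.

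**Conclusion.** The point holds as an internal inconsistency with a possible cost to the primary endpoint. The listed criteria permit entry after about month 4.16 of a six-month isoniazid course, while the primary endpoint and the two-month follow-up statements need treatment to continue to week 8.

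If late entrants are enrolled, the consequence is dilution and lost power. Relative to the 69% baseline, the loss is about 11 percentage points at f = 5%, 20 at 10%, 39 at 25% and 52 at 46%. It is zero if all enter at about month 2. The gap between the planned 80% and 69% belongs to the sample-size calculation and should not be charged to this point.

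These figures assume that late entrants finish on schedule, that all of them test negative at week 8, that f is equal in the two arms, and that the planning rates hold for everyone else.

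**What to change.** Reconcile the inclusion criteria, exclusion criteria and Recruitment section with the Abstract, Intervention group, Control group, Outcome and Implementation sections. Trial eligibility should require that scheduled isoniazid-containing treatment continues through the week-8 test, that is, at least eight weeks remain at randomisation. The Recruitment section should say whether patients are identified in the intensive phase and entered once it is complete.

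This is an entry rule only and changes no one's treatment. The cost is a one-line amendment and the loss of late-course patients, who cannot yield a valid primary endpoint. It should be in place before enrolment, because the intention-to-treat analysis retains anyone already randomised. If enrolment has begun, tabulate the treatment month at entry by arm so that f is known.
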